### Statistical considerations

For sample and power calculations, this study is powered based on changes in hemoglobin A1c in RCTs included in the meta-analysis by Zuuren et al. (2018), which tested the effect of carbohydrate restriction up to 8 weeks. Considering a type I error of 5% and a power of 80% to detect differences at the dependent variable with a statistical significance when comparing 3 independent groups (CTRL versus EH and EH versus EH + LCD), and an effect size of 1.14, a sample size of 14 participants per group will be needed, totaling 42 individuals. With an assumption of a 20% dropout rate, we will recruit 48 participants. The sample size calculations were performed using the Statistical Power Analyses for Windows, (G*Power 3.1.9.4, Uni Kiel, Germany).

Statistical analysis will be performed using SPSS statistics software version 28.0, 2021 (IBM Company, Chicago, United States). All data will be reported as mean ± SD and statistical significance will be assumed at *p* ≤ 0.05. Pairwise comparisons will be analyzed using the Wilcoxon test. A two-way repeated measures ANOVA will be used to examine changes in cardiopulmonary parameters, body composition, glycemic profile, and cardiovascular risk factors over the chronic exercise period (0 vs. 8 weeks), and whether the magnitude of the chronic exercise-mediated adaptations differ between groups (EH vs. CTRL; LCD + EH vs. EH). When a significant main- or interaction-effect will be found, Bonferroni post hoc tests for multiple pairwise comparisons will be performed to identify differences between groups.

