### Assignment of intervention

Participants confirmed as eligible will be randomized at a ratio of 1:1:1 to each group in blocks of four participants until complete the total number calculated (*n* = 48). A computer-generated random numerical sequence will be used for randomizing participants (Research Randomizer). The principal researcher will generate the sequence and conceal it in sealed, numbered opaque envelopes. Participants will be allocated a sequential number upon screening. The sealed envelope corresponding to the allocated participant number will be opened on the first visit by the principal researcher, and the participants will be allocated, without knowing which group they will belong to. As this is a single-blind study, blinding is not required for principal researcher, only to participants. A Consolidated Standards of Reporting Trials (CONSORT) flow chart outlining the study phases is displayed in Figure 2 (Moher et al., 2001).

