### Study outcomes

The main outcome will be hemoglobin A1c levels after 8 weeks of interventions. A set of secondary clinical outcomes will include complete blood count with hemoglobin and reticulocytes, fasting glucose, fasting insulin, HOMA-IR, total-, LDL- and HDL-cholesterol levels, triglycerides, C-reactive protein, serum HIF1-α levels, systolic and diastolic blood pressure, body composition, cardiorespiratory and pulmonary gas-exchange variables. These outcomes will be evaluated at baseline and at the end of the study (eighth week), in all groups.

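### The 80% power belongs to one unadjusted two-group test; under the plan's own Bonferroni pairwise analysis it is about 74–75% per contrast (two contrasts) or 68–70% (three pairs) at 14 per group

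*Protocol article*

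**What the plan says.** HbA1c is the single main outcome (Study outcomes: "The main outcome will be hemoglobin A1c levels after 8 weeks of interventions"). In Statistical considerations, the first paragraph sets 5% type I error and 80% power "when comparing 3 independent groups (CTRL versus EH and EH versus EH + LCD"), and gives "an effect size of 1.14, a sample size of 14 participants per group will be needed, totaling 42 individuals". The effect size is "powered based on changes in hemoglobin A1c in RCTs included in the meta-analysis". On recruitment: "With an assumption of a 20% dropout rate, we will recruit 48 participants", which is 16 per arm.

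The second paragraph plans a two-way repeated measures ANOVA (0 vs 8 weeks) and names the same two contrasts, EH vs CTRL and LCD + EH vs EH. If a main effect or an interaction is significant, "Bonferroni post hoc tests for multiple pairwise comparisons will be performed to identify differences between groups". A separate sentence assigns pairwise comparisons to the Wilcoxon test without mentioning adjustment. The article gives no order of testing for the two contrasts and does not say whether Bonferroni runs over two comparisons or three.

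**The concern.** The two paragraphs describe different tests. The sample-size paragraph spends the full 5% on one comparison of two groups, while the analysis paragraph divides it among several pairwise comparisons. A design figure should describe the test that will be used to declare a difference. Here the stated power for the main outcome is higher than the stated analysis delivers. The Summary section already concedes that an HbA1c difference between EH and EH + LCD may be hard to show. Overstated power makes an inconclusive result easier to misread as evidence of no effect.

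**Working it through.** **Inputs.** From Statistical considerations: effect size d = 1.14, type I error 0.05, n = 14 per group, 48 recruited, 20% dropout. Two-sided testing is assumed, because the sidedness is not stated and one-sided 5% would need only 11 per group.

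**Formula.** For two groups of n, the noncentrality is δ = d·√(n/2) and power = P(|T| > t₁₋α/₂) for a noncentral t with df = 2n − 2, or 3n − 3 if the error variance is pooled over three arms.

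**Step 1: reproduce the plan's figure.** At α = 0.05:
- n = 13: δ = 1.14·√6.5 = 2.906, power 0.796.
- n = 14: δ = 1.14·√7 = 3.016, critical t (26 df) = 2.056, power 0.827.

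So 14 per group is the smallest size reaching 80% for one unadjusted two-group test.

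**Step 2: try readings that involve all three groups.** None gives 14.

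| Reading | n per group for 80% |
|---|---|
| Three-group ANOVA, f = 1.14 | 4 |
| ANOVA, f = 1.14/2 = 0.57 | 11 |
| ANOVA, extreme groups 1.14 SD apart, middle group halfway (f = 0.465) | 16 |
| ANOVA, one group 1.14 SD from the other two (f = 0.537) | 13 |
| ANOVA, adjacent groups 1.14 SD apart (f = 0.931) | 5 |
| t-test, Bonferroni over two (α = 0.025) | 16 |
| t-test, Bonferroni over three (α = 0.0167) | 18 |

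A Wilcoxon–Mann–Whitney calculation (efficiency 0.955 relative to the t-test) also gives 14, with power 0.808. It is therefore clear that the calculation was one unadjusted two-group test; that it was a t-test is only the most natural reading.

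**Step 3: power per contrast under Bonferroni.** At n = 14, δ stays at 3.016, but the critical t (26 df) rises from 2.056 to 2.379 (α = 0.025) or 2.559 (α = 0.0167). In each cell below, the first value uses two-group df and the second uses pooled df.

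| n per arm | α = 0.05 | α = 0.025 (two contrasts) | α = 0.0167 (three pairs) |
|---|---|---|---|
| 14 (planned) | 0.827 / 0.837 | 0.735 / 0.751 | 0.675 / 0.695 |
| 12.8 (16 × 0.8) | 0.790 / 0.801 | 0.687 / 0.705 | 0.623 / 0.645 |
| 16 (all complete) | 0.877 / 0.884 | 0.801 / 0.814 | 0.750 / 0.766 |

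**Step 4: does repeated measurement rescue the figure?** With two time points, the group-by-time contrast is a comparison of change scores. The effect size is itself described as coming from HbA1c changes, so on that reading the model adds nothing to the table.

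**Step 5: type I error if the contrasts were left unadjusted.** Three arms of 14 were simulated with pooled error. Two 5% contrasts tested directly give a familywise error of 9.0%. Tested only after a significant three-group F test on change (equivalent to the group-by-time interaction), they give about 4.3% when there is no effect anywhere, and about 5% on the null contrast when the other effect is real. Power is then 0.80 for a single true contrast, and 0.84 for each contrast when both are true.

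**The case against.** The strongest reply is that the plan does not test contrasts freely: pairwise tests follow only a significant effect. A reader might infer that the trial must accept either power well below 80% or a familywise error of about 9%. The documents do not support that either/or. The 9% applies to ungated tests; step 5 shows that unadjusted contrasts gated on the interaction hold roughly 5% and 80% at 14 per group. Two limits remain. The plan puts Bonferroni on top of the gate, and that costs power. Its gate also opens on a main effect: all three arms exercise, so a main effect of time could appear without any difference between groups, and such a gate would not protect unadjusted contrasts.

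A second reply is that the plan names only two contrasts and that 62% is reached only by combining three-pair Bonferroni with dropout. That is correct. Whether 48 is enough to cover 20% dropout is a separate matter. For multiplicity alone, with two contrasts at 14 per group, the loss is about 9 points (0.827 to 0.735, or 0.837 to 0.751 pooled). If nobody drops out, two-contrast Bonferroni still reaches 80%.

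Third, the article never labels either contrast primary and speaks of one primary hypothesis, so it makes no claim about winning both contrasts. That stands, and no joint power is charged against it here. The statement that both comparisons are powered is nevertheless the article's own.

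Finally, the Wilcoxon sentence could mean that unadjusted tests decide. This would add to the ambiguity about which test governs; it would not remove the Bonferroni sentence.

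**Conclusion.** The point holds as a mismatch between the design calculation and the stated analysis. The sample-size arithmetic itself reproduces. Under the stated Bonferroni analysis, power per contrast at 14 per group is about 74–75% for the two named contrasts, or about 68–70% if all three pairs are adjusted for. With 20% dropout this becomes about 69–71% or 62–65%; with full completion, about 80–81% or 75–77%.

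These figures assume two-sided tests, roughly normal data, 1.14 as a standardized difference in HbA1c change, and the same 1.14 for each contrast. The last assumption is generous for CTRL vs EH, because the effect size comes from carbohydrate-restriction trials and those two arms share the same diet. A reader might go further and conclude that the true power is 62% or that the type I error is uncontrolled. The first is only the least favourable conditional case, and the second does not follow from the plan as written.

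**What to change.** State that the HbA1c group comparison consists of the two named contrasts only, and replace the generic pairwise Bonferroni with one rule fixed in advance:
- Holm or Bonferroni over the two contrasts;
- a fixed testing order, each at 5%; or
- unadjusted 5% contrasts, tested only after a significant group-by-time interaction and not after a main effect.

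Say which test (model contrast or Wilcoxon) decides. Then restate power under the chosen rule at the expected completers; for Bonferroni over two at 12.8 per arm this is about 69–71%.

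Analysing week-8 HbA1c by ANCOVA with baseline as covariate would recover part of the loss. Relative to change scores, the variance is multiplied by (1 + ρ)/2, where ρ is the baseline–week-8 correlation. The documents do not give ρ. Assuming 0.8 to 0.5, the effective d is 1.14/√0.90 = 1.20 to 1.14/√0.75 = 1.32. Power at α = 0.025 and 14 per arm is then about 0.76 to 0.84, using two-group df and allowing for estimation of the covariate.

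The cost is wording and a less favourable stated power. No extra patients are needed.

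### Recruiting 48 participants does not cover the stated 20% dropout: about 38 would complete against the 42 required, and 48 covers only 12.5%

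*Protocol article*

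**What the plan says.** The section *Statistical considerations* of the protocol article gives the whole calculation in two consecutive sentences. The design values are a 5% type I error, 80% power and an effect size of 1.14, for the situation "when comparing 3 independent groups (CTRL versus EH and EH versus EH + LCD"). The result is that "a sample size of 14 participants per group will be needed, totaling 42 individuals". The allowance for loss follows: "With an assumption of a 20% dropout rate, we will recruit 48 participants".

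The figure of 48 is used consistently elsewhere. The abstract gives it, *Study design and setting* gives 16 per group, and *Assignment of intervention* gives it again as the total to be randomised 1:1:1. No section gives another dropout rate, says that dropouts will be replaced, or explains the step from 42 to 48.

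**The concern.** The required number, the dropout rate and the recruitment target are all stated, so any two of them fix the third. Here the third does not follow. Under *Study outcomes*, the primary outcome, hemoglobin A1c, is measured at baseline and at the eighth week only, so a participant lost before week 8 contributes no post-baseline value. If the dropout assumption is right, the trial ends with fewer participants than its own calculation calls for. The 80% power is then not the power of the trial at the dropout that the article assumes. A reader who takes the sentence at face value will believe that a 20% loss has been provided for.

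**Working it through.** **Inputs** (all from *Statistical considerations*, except the 16 per group from *Study design and setting*): type I error 5%; power 80%; effect size 1.14; 14 per group, 42 in total; dropout 20%; 48 recruited, 16 per group. The article states neither whether the test is one- or two-sided nor which kind of effect size is meant.

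**Step 1: reproduce the required number.** Take a two-sided two-sample t-test at 5% with standardised mean difference d = 1.14. With n per arm, the noncentrality is d × √(n/2) on 2n − 2 degrees of freedom.

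- n = 13: 1.14 × √6.5 = 2.906, 24 df, power 0.796, just short of 80%.
- n = 14: 1.14 × √7 = 3.016, 26 df, power 0.827.

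So 14 per arm and 3 × 14 = 42 in total are reproduced. Other readings do not fit: a one-sided test needs only 11 per arm (power 0.826), and reading 1.14 as an ANOVA effect size f needs only 12 participants in total. The two-sided t-test with d = 1.14 is therefore a reasonable inference. A Wilcoxon–Mann–Whitney calculation also gives 14 (power 0.808).

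**Step 2: reproduce the recruitment target.**

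| Rule | Calculation | Result |
|---|---|---|
| Divide by the completion rate, total | 42/(1 − 0.20) = 52.5 | 53 |
| Divide by the completion rate, per arm | 14/0.80 = 17.5, so 18 | 54 |
| Add 20%, total (a common shortcut, too low) | 42 × 1.20 = 50.4 | 51 |
| Add 20%, per arm (same shortcut) | 14 × 1.20 = 16.8, so 17 | 51 |
| Stated | – | 48 |

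None of these rules gives 48.

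**Step 3: what 48 does cover.**

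- Expected completers at 20% dropout: 48 × 0.80 = 38.4; per arm 16 × 0.80 = 12.8.
- Largest dropout that still leaves 42: 1 − 42/48 = 12.5%.
- As an add-on to 42: 48/42 − 1 = 14.3%.
- If each participant drops out independently with probability 0.20, the chance that at least 42 of 48 complete is about 13%.

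**Step 4: power at the completer numbers** (the test of Step 1, one unadjusted comparison; the Wilcoxon–Mann–Whitney column uses the asymptotic relative efficiency 3/π).

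| Completers per arm | t-test | Wilcoxon–Mann–Whitney |
|---|---|---|
| 14 | 0.827 | 0.808 |
| 13 | 0.796 | 0.776 |
| 12.8 | 0.790 | 0.769 |
| 12 | 0.761 | 0.740 |

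**The case against.** The best defence is that the error hardly matters. Rounding up to 14 per arm had already put power above the target, so at the expected 12.8 per arm the t-test falls only about one percentage point short of 80%. The planned analysis is also an ANOVA over the groups. If its error term is pooled over all three arms (an assumption: equal variances, 3n − 3 degrees of freedom), power at 12.8 per arm is 0.801 and the target is still met. This stands, and it limits how serious the point is. It does not make the sentence correct, because the mismatch between 38.4 and 42 depends on no choice of test.

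A reader might also infer a much larger loss by bringing in the Bonferroni post hoc tests. With three pairwise comparisons (alpha 0.0167), power at 12.8 per arm is 0.62. The documents do not support attributing that figure to the dropout error. With the full 14 per arm, the same adjustment already gives 0.675, so the dropout shortfall accounts only for the step from 0.675 to 0.623. The number of comparisons is not settled either: the article names two contrasts, and with two (alpha 0.025) the figures are 0.735 at 14 and 0.687 at 12.8. Most of the fall comes from multiplicity, which is a separate issue.

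**Conclusion.** The statement is wrong as written. Of 42 required, 20% dropout and 48 recruited, at least one must change. At the stated dropout the trial expects 38.4 completers, 3.6 fewer than required (1.2 fewer per arm), and 48 provides for 12.5% and not for 20%. That conclusion is plain arithmetic and needs no assumption about the test.

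The effect on power is modest: from 0.83 to about 0.79 for one unadjusted comparison, with a range of 0.76 to 0.80 for 12 to 13 completers per arm. These figures rest on the inferred two-sided t-test with d = 1.14 and on dropouts contributing no week-8 value. They do not support a claim that the trial is seriously underpowered because of this error. It is a correction that should be made to a stated figure.

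**What to change.** Keep 48 and correct the sentence in *Statistical considerations*, in one of two ways:

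- *Recruiting 48 participants allows for a dropout of 12.5%*; or
- *With 20% dropout, about 38 completers (12–13 per arm) are expected, giving about 76–80% power for one unadjusted comparison.*

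The second is more informative if 20% is still the team's realistic expectation. In that case, the type of effect size and the two-sided test should be stated with it, so that the power figure can be checked.

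The cost is wording only, and the stated power becomes slightly less favourable. Raising the target to 54 (18 per arm) would honour the 20%, but it needs six more participants, and the *Recruitment* section has recruitment ending in September 2023. The small loss in power does not require it.

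### The named repeated-measures ANOVA on HbA1c is, with two time points, an unadjusted change-score test: it loses precision and is open to regression-to-the-mean bias if dropout depends on baseline differently by arm

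*Protocol article*

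**What the plan says.** All references are to the protocol article.

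- **Outcome (Study outcomes).** "The main outcome will be hemoglobin A1c levels after 8 weeks of interventions". On timing: "These outcomes will be evaluated at baseline and at the end of the study (eighth week), in all groups". No intermediate HbA1c measurement is planned.
- **Analysis (Statistical considerations).** "A two-way repeated measures ANOVA will be used to examine changes in cardiopulmonary parameters, body composition, glycemic profile, and cardiovascular risk factors", comparing week 0 with week 8, in SPSS 28. HbA1c belongs to the glycemic profile, so this covers the main outcome. Two contrasts are named: hypoxia exercise against control, and hypoxia exercise plus low-carbohydrate diet against hypoxia exercise alone. No baseline covariate is named.
- **Dropout (Statistical considerations).** "With an assumption of a 20% dropout rate, we will recruit 48 participants".
- **Framework (Data collection and management).** The primary hypothesis is tested for superiority, and withdrawals are documented qualitatively.

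**The concern.** A repeated-measures ANOVA sounds as if it uses the baseline fully. With exactly two visits it does not: its group-by-time test reduces to a one-way ANOVA on week 8 minus week 0. This has two consequences.

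1. **Bias.** A high baseline tends to fall and a low one to rise, whatever the treatment. If participants with high baseline HbA1c leave one arm more readily than another, the remaining groups differ in expected change even when the treatments do not differ. A change-score comparison takes that difference for a treatment effect; a baseline-adjusted model does not.
2. **Precision.** Subtracting the whole baseline value over-corrects unless the correlation between the visits is 1. In a trial with 16 participants per arm this matters even if nobody drops out.

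At stake are the size and the standard error of the HbA1c contrast on which the superiority conclusion rests.

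**Working it through.** **1. The plan's own figure.** The protocol gives "Considering a type I error of 5% and a power of 80% to detect differences" and "an effect size of 1.14, a sample size of 14 participants per group will be needed, totaling 42 individuals". A two-sided two-sample t-test (noncentral t, alpha 0.05, d = 1.14) needs 14 per group, with power 82.7%. The stated figure reproduces. It is a two-group comparison of means with no baseline adjustment.

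**2. What the stated dropout leaves.** 48 × 0.20 = 9.6 lost and 38.4 remaining, or 12.8 per arm, with power about 79.0%. Power hardly moves, so power loss from dropout is not the issue here.

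**3. The test.** With baseline B and week-8 value Y, the group-by-time F test equals a one-way ANOVA on D = Y − B. If Y is missing, D is missing.

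**4. Bias under baseline-dependent dropout.** All inputs in this step except the 20% are assumed, since the documents give no SD or correlation: SD 0.9 at both visits, correlation ρ of 0.5 or 0.7, 20% dropout per arm, no true effect. Dropout depends on baseline in one arm only, with logit slope s = 0.7 to 1.5 per SD (odds ratio e^0.7 = 2.0 to e^1.5 = 4.5).

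- Expected change given baseline: E(D | B) = −(1 − ρ)(B − μ).
- Completers' baseline shift in SD units: m = E[Z(1 − p(Z))] / 0.8, with Z standard normal, p(Z) = 1/(1 + exp(−(a + sZ))) and a set so that the mean of p is 0.20. Numerical integration gives m = −0.130 at s = 0.7 and −0.227 at s = 1.5.
- Bias of the change-score contrast: |m| × (1 − ρ) × 0.9.

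| s | ρ = 0.7 | ρ = 0.5 |
|---|---|---|
| 0.7 | 0.130 × 0.3 × 0.9 = 0.035 | 0.130 × 0.5 × 0.9 = 0.058 |
| 1.5 | 0.227 × 0.3 × 0.9 = 0.061 | 0.227 × 0.5 × 0.9 = 0.102 |

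Large-sample simulations of the same scenarios agree (about 0.03 to 0.10 HbA1c points). A baseline-adjusted model fitted to **the same completers** is off by 0.003 or less. So it is the lack of adjustment, and not the loss of participants, that produces this bias.

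**5. Precision.** With equal variances σ² at the two visits:

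- change score: Var(D) = 2σ²(1 − ρ);
- baseline-adjusted: residual variance = σ²(1 − ρ²);
- ratio = (1 + ρ)/2 = 0.75 at ρ = 0.5 and 0.85 at ρ = 0.7.

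Ignoring the small cost of estimating one slope, 12.8 completers per arm analysed with adjustment are worth 12.8/0.85 = 15.1 to 12.8/0.75 = 17.1 per arm analysed as change scores.

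**6. What adjustment does not cure.** If dropout in one arm depends on the response itself (logit slope 0.5 to 1.0 per SD of change), the change-score contrast is shifted by about 0.09 to 0.17 SD of change, and an adjusted model still keeps about 0.07 to 0.15 SD. In small-sample simulations of the change-score test (16 per arm, no true effect, all inputs assumed):

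- dropout unrelated to outcome: bias about 0, type I error 5.0%;
- outcome-related and alike in both arms at 20%: −0.01 SD, 5.1%;
- outcome-related in one arm only, 20% in each: −0.17 SD, 6.9%;
- outcome-related in one arm only, 30% against 10%: −0.26 SD, 9.6%.

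**The case against.** The strongest reply is that this is a missing-data complaint in disguise. The article names a model but no analysis set and no missing-data rule; imputing before a repeated-measures ANOVA would fit its text; and such rules commonly sit in a full protocol or SAP that is not shown. This stands as far as it goes.

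For that reason a tempting stronger reading fails. A reader might infer that the protocol commits to a completers analysis, so that the superiority claim rests on a subset selected after randomisation. The documents do not support this:

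- The article nowhere limits the analysis to completers, and inflating a sample size for dropout does not define an analysis set. Recruiting 48 to keep 42 is in any case a 12.5% allowance (1 − 42/48), not 20%; that is a separate point.
- Nothing says that participants who stop training or diet go unmeasured at week 8. If measured, they stay in the ANOVA. The limitations in the Summary speak of non-adherence to the diet leading to inclusion of patients with higher carbohydrate intake, which points towards keeping them.
- No passage predicts different dropout by arm. Altitude side effects can arise only in the hypoxia arms, so it is plausible, but staff training for possible side effects is not a forecast of loss.

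The size can also be challenged. A bias of 0.035 to 0.102 points is 0.13 to 0.29 of the standard error at 12.8 per arm. It is about 4% to 10% of the planned effect, if 1.14 is read in SDs of change (0.79 to 1.03 points under the same inputs). That is fair: the bias is modest and conditional.

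What survives is the choice of method. The article states an unadjusted change-score test, and a better one uses data already planned for collection.

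**Conclusion.** The point holds as a criticism of the named model. That the group-by-time test is an unadjusted change-score comparison follows from the protocol's text without further assumption. The loss of precision needs no dropout: the adjusted residual variance is about 0.75 to 0.85 of the change-score variance if the correlation is 0.5 to 0.7 and the variances are equal. The bias of about 0.03 to 0.10 HbA1c points is conditional on 20% dropout that depends on baseline in one arm only, with an assumed SD, correlation and odds ratio. It vanishes if dropout is unrelated to baseline or acts alike in the arms compared. Bias from dropout that depends on the unobserved response is a further risk, which a change of model only partly reduces.

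**What to change.** 1. For the two named contrasts, replace the repeated-measures ANOVA on HbA1c with a linear mixed model of the baseline and week-8 values with a common baseline mean across arms (SPSS MIXED), or with ANCOVA on week-8 HbA1c adjusted for baseline. Analyse by randomised arm and include all randomised participants with available data.
2. State that the planned week-8 sample is also taken from participants who stop training or diet but have not withdrawn consent.
3. Add a sensitivity analysis for dropout that depends on the unobserved week-8 value, since about 0.07 to 0.15 SD remains after adjustment in the assumed scenarios.

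The cost is a change of analysis wording and slightly more analysis work in the software already named; the blood sample is already planned. The effect estimate may be somewhat smaller, because participants who stop the intervention stay in the comparison.

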### Data collection and management

A questionnaire will be applied in the first nutrition appointment, at the beginning of the study, to obtain the eating habits, socio-demographic and clinical characteristics of participants, including age, sex, marital status, schooling level, diabetes duration, family history of diabetes and self-reported physical activity. Drugs for T2DM or comorbidities and nutritional supplements will be registered at baseline and at the end of the study.

Blood samples will be collected and centrifuged at 1000 g for 10 min to separate plasma or serum, which will be stored at −80 °C for further analysis of biochemical parameters.

During the intervention period, the team of researchers will be trained to apply the 24-h food recall, constantly checked the oxygen saturation and supervise the maintenance of the heart rate at the target intensity of 75% of the heart rate reserve. All researchers will be trained to circumvent any cases of hypoglycemia, hypotension or possible side effects of high-altitude exposure, such as headache or difficulty breathing. Also, it will be qualitatively documented and details of each case of withdrawal and, the primary hypothesis will be tested on a superiority framework.

All data will be collected and stored according to Good Clinical Practice Guidelines (Switula, 2000). Data monitoring and auditing of the trial will be conducted by the principal researcher and supervisory team: [name], [name] and [name] All data, such as consent forms, questionaries, dietary screening forms, IPAQ and clinical data in general, will be stored in a secure database password-protected document that will be accessed only by authorized members of the research team. Dietary plans will be stored securely in Dietbox® Software, and all information will be treated confidentially. Data will only be used for the purpose of this research project.

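### The post hoc rule for HbA1c is triggered by effects that do not measure treatment, leaves its contrast open and gives Wilcoxon no defined role; a baseline-adjusted ANCOVA on the two named contrasts should decide

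*Protocol article*

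**What the plan says.** Under Study outcomes, the protocol article fixes the primary endpoint: "The main outcome will be hemoglobin A1c levels after 8 weeks of interventions". On timing it adds: "These outcomes will be evaluated at baseline and at the end of the study (eighth week), in all groups". There are therefore two measurements per patient.

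Under Statistical considerations, a two-way repeated measures ANOVA is applied to every outcome group, glycemic profile included. Its group question is whether the size of the change differs between arms, for EH against CTRL and for LCD + EH against EH. Two sentences then govern the pairwise tests:

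- "Pairwise comparisons will be analyzed using the Wilcoxon test". The text does not say whether these are paired within-arm or independent between-arm tests, what adjustment applies, or whether the result decides anything.
- "When a significant main- or interaction-effect will be found, Bonferroni post hoc tests for multiple pairwise comparisons will be performed". The stated purpose is to find differences between groups.

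The sample size is set "when comparing 3 independent groups (CTRL versus EH and EH versus EH + LCD"), with "an effect size of 1.14, a sample size of 14 participants per group will be needed, totaling 42 individuals". No baseline covariate is mentioned.

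**The concern.** With two time points, the three terms of the ANOVA answer different questions.

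- **Time** is the average change over all arms. All three arms train, so a common fall in HbA1c is expected whether or not hypoxia or diet adds anything.
- **Group** compares means averaged over baseline and week 8. Randomised arms differ at baseline only by chance, so averaging halves a week-8 difference and adds baseline noise.
- **Interaction** compares changes between arms. It is the only term that answers the protocol's own question.

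The rule treats all three as grounds for between-group tests and does not tie those tests to the change or the week-8 difference. The Wilcoxon sentence puts a second method under the same name. What is at stake is which test decides the primary outcome: one reading has adequate power and controlled error, another has little power, and a third has error above 5%.

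**Working it through.** **Inputs from the protocol.** 14 per arm, three arms, effect size 1.14, alpha 5%, power 80%, two named contrasts. Superiority is stated but sidedness is not; two-sided is assumed.

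**Assumptions, not in the protocol.** Correlation r between baseline and week-8 HbA1c of 0.5, 0.7 or 0.8; equal SD at both times (set to 1); 1.14 taken as the difference in SDs of change; a common fall of 0.5 baseline SD where a time effect is needed.

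**1. The protocol's own figure.** A two-sample t-test with d = 1.14 at two-sided 0.05 and 80% power needs 13.11 per arm, rounded up to 14. Power at 14 is 82.7%. The stated 14 is reproduced, as a single comparison at the full 5%.

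**2. How often a main effect triggers.** SD of change = √(2(1 − r)), which is 1.0 at r = 0.5. For a common fall of 0.5 in 42 patients the noncentrality is 0.5 × √42 / 1.0 = 3.24, so the time effect is significant in 88% of trials at r = 0.5 (98% at 0.7, 99.9% at 0.8) with no difference between arms.

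**3. Whether that produces false claims.** In three-arm simulation with a common fall and no group difference, Bonferroni tests at 0.05/3 gave at least one false claim among all three pairs in 4.0–4.4% of trials, on either change scores or time-averaged means. For the two named contrasts the figure is about 3%. A single fixed family therefore stays below 5% even though the trigger is nearly always met.

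**4. Effect size under each possible contrast.**

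| Contrast | Standardised effect | r = 0.5 | r = 0.7 | r = 0.8 |
|---|---|---|---|---|
| Change | 1.14 | 1.14 | 1.14 | 1.14 |
| Time-averaged mean | 1.14 × √((1 − r)/(1 + r)) | 0.66 | 0.48 | 0.38 |
| ANCOVA | 1.14 × √(2/(1 + r)) | 1.32 | 1.24 | 1.20 |

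The second row is half the week-8 effect, 0.5 × 1.14 × √(2(1 − r)), over the SD of the average, √((1 + r)/2). The third is the full week-8 effect over the residual SD, √(1 − r²).

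**5. Power for one contrast, 14 per arm** (noncentrality = effect × √(14/2)).

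| Test | Alpha | r = 0.5 | r = 0.7 | r = 0.8 |
|---|---|---|---|---|
| Time-averaged mean (two arms, 26 df) | 0.0167 | 22.7% | 11.6% | 7.5% |
| Change (three-arm error, 39 df) | 0.0167 | 70% | 70% | 70% |
| Change (39 df) | 0.025 | 75% | 75% | 75% |
| ANCOVA (three-arm simulation) | 0.025 | 86% | 81% | 79% |

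The ANCOVA variance is (1 + r)/2 of the change-score variance: 0.75 at r = 0.5 and 0.90 at r = 0.8. The formula alone, ignoring chance baseline imbalance, gives 87%, 82% and 80%.

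**6. Wilcoxon.**
- If between-arm: two tests at 0.05 each would give 1 − 0.95² = 9.75% familywise error if independent. They share the EH arm, and simulation gives about 9%. Free choice between Wilcoxon and any version of the Bonferroni tests gives 12.5–13%.
- If within-arm: when two arms improve equally by 0.4–0.8 SD of change, one is significant and the other not in 36–49% of trials.

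**7. Familywise error after the fix.** ANCOVA with two contrasts at 0.025 each gives 4.3–4.9%.

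**The case against.** The strongest reply has four parts.

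First, a reader might infer that the main-effect trigger itself creates false positives, because it is met in 88% or more of trials. It does not. A claim still needs a Bonferroni-significant contrast, and step 3 shows that error stays below 5%. Nor does it cost power, because a significant interaction (about 86% power here) also opens the tests. This part stands in full.

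Second, a reader might infer that the trial as written has only 8–23% power. That holds only if the post hoc tests use time-averaged means. The protocol does not say so, and its stated question concerns change. This stands too: the figure shows what an unspecified contrast could cost, not what the plan commits to.

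Third, if Wilcoxon means within-arm before/after testing, it answers a different question from the between-group Bonferroni tests and does not conflict with them. It misleads only if group differences are inferred from it. If it means between-arm testing, the 36–49% discordance does not apply. What survives is that the sentence has no stated role, and that the between-arm reading carries no stated adjustment.

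Fourth, the interaction is a valid comparison of change scores, the sample size is based on changes in HbA1c, and a separate analysis plan may add covariates. All true. ANCOVA is the more efficient choice, not the only valid one, and at r = 0.8 the gain is small (79% against 75%). However, the post hoc rule and the Wilcoxon sentence are stated in the protocol, so correcting them is not a request for omitted detail.

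**Conclusion.** The point holds in a limited form. The decision rule accepts main effects of time and group, which do not measure the treatment effect. It does not tie the post hoc tests to change or week-8 HbA1c, and it leaves a Wilcoxon test with no role or adjustment beside the Bonferroni tests. One prespecified Bonferroni family on change would be valid, with about 70% power at 0.0167 or 75% at 0.025. The other readings that the wording allows are worse: about 23% to 8% power on time-averaged means, or about 9% familywise error with two unadjusted between-arm Wilcoxon tests.

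The documents do not support saying that the plan produces invalid claims as written, or that repeated measures ANOVA is wrong here. This is a correction worth making before analysis, not a fatal flaw. The time-averaged and ANCOVA power figures rest on the assumed correlation of 0.5–0.8, and all power figures take 1.14 as SDs of change with two-sided tests. Across that range the order of the methods does not change.

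**What to change.** 1. Make the primary analysis an ANCOVA of week-8 HbA1c on arm with baseline HbA1c as covariate.
2. Test only the two named contrasts, CTRL against EH and EH against EH + LCD, at a Bonferroni 0.025 each. Report adjusted mean differences with confidence intervals.
3. Delete the main-effect trigger. If the repeated measures ANOVA is kept, base between-group statements on the interaction, as contrasts of change.
4. Confine Wilcoxon to descriptive within-arm summaries or a labelled sensitivity analysis, and state that no between-group claim rests on within-arm tests.

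The cost is analysis wording only: baseline and week-8 HbA1c are already collected, and no extra patients or visits are needed. At 14 per arm the change raises power from 75% (change scores at 0.025) to between 79% and 86% over the assumed correlations.
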